**Treatment composition**	
**Component**	**Quantity**
Bifidobacterium animalis subsp. lactis BS01	≥ 1 x 10^9^ CFU
Bifidobacterium longum 03	≥ 1 x 10^9^ CFU
Bifidobacterium adolescentis BA02	≥ 1 x 10^9^ CFU
Fructo-oligosaccharides FOS	2500 mg
Maltodextrin	q.s.
**Placebo composition**	
**Component**	**Quantity**
Maltodextrin	q.s.

Follow-up visits will be scheduled at 6 weeks after T0 (T1) and at 12 weeks after T0 (T2). At T1, physical and neurological examination will be repeated, and all clinical scales administered again, except for Bristol Stool Form Chart and MOCA. At T2, all assessments performed at T0 will be carried out again, including blood withdrawal.

Participants will be advised to report any suspected adverse reaction and new or worsening symptoms. Every report will be recorded, and a thorough evaluation will be performed by neurologists in the clinical staff in collaboration with the subject’s primary care doctor. Feedback will be provided to the participant as well as indications on continuing or stopping treatment administration. In accordance with the Declaration of Helsinki by the World Medical Association, every participant can freely request to be removed from the study at any moment. All participants will be requested to record daily treatment usage and keep empty packaging or unused doses for recollection after the trial completion. One courtesy call will be scheduled during treatment to reduce compliance issues. The use of immunomodulating drugs or antibiotic therapy is an exclusion criterion and patients starting such therapy during the trial period will be dropped from the study. Dose adjustments in antiparkinsonian therapy are permitted but should be avoided and substantial modifications to said therapies will cause dropping out from the study.

Every participant will be evaluated at enrolment by a clinical neurologist, who will assess needed adjustments in antiparkinsonian therapy that will be completed within two weeks from enrolment and before treatment administration to minimise the need for medical therapy modifications during the trial. The use of laxative or prokinetic drugs will be recorded and is not an exclusion criterion per se, but the introduction of these medications or posology variations should be avoided during the trial.

### Outcomes

#### Primary feasibility outcomes

To assess the feasibility of the proposed clinical trial, we defined different feasibility objectives, as previously listed in Table 1.

More in detail, we will evaluate the potential recruitment rate for the clinical trial by recording the number of eligible outpatients who scheduled a neurological examination in the proposed clinical setting during the pilot trial. The acceptance rate will also be evaluated, by recording the fraction of identified eligible subjects who will be willing to participate in the proposed clinical trial. Both assessments together will allow for an initial estimate of the needed duration for the main clinical trial, once an appropriate sample size will be defined based on the pilot trial results. During the pilot trial, the dropout rate will also be recorded to adjust the predicted trial duration based on the fraction of dropped-out subjects during the trial period.

Reported reasons for subject drop-out will also be recorded and further analysed to confirm the safety of both the treatment and placebo administration to enrolled subjects. Collected data during the pilot trial will be analysed to assess whether a significant variation in any recorded parameter will occur between the two trial branches. This will allow to accordingly select one or more appropriate primary outcomes for the main trial, among collected immune profile data. Secondary outcomes for the main trial will be selected in the same way, among parameters who will show a remarkable variation.

More in detail, in our previous in vitro study (Magistrelli et al., 2019), we demonstrated that probiotics modulate ROS and cytokine production by driving an anti-inflammatory profile. Therefore, we will test whether these properties are confirmed in vivo. Particularly, in our study, we want to analyse whether probiotics may modulate cytokines production, such as IFN-γ, TNF-α, IL-4, IL-10, and ROS production.

In order to investigate possible changes in immune phenotype, we plan to deepen the profile of both innate and adaptive immunity by means of a cytofluorimetric evaluation, according to the strategy described by Kustrimovic et al. (2018) and with additional panels specifically dedicated to innate immunity. The following cell subsets of the adaptive immune system will be assessed: CD4+ and CD8+ T naïve/memory cells, CD4+ T helper subsets (Th1, Th2, and Th17), and CD4+ regulatory T cells (conventional, naïve, and activated Treg). Moreover, for innate immunity, monocytes (classical, non-classical, and intermediate), and NK cells (NK CD56 dim and CD56 bright) will be also assessed. We will compare pre-treatment and post-treatment analysis and compare our intervention group with the placebo group at T0 and T2.

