#### Objectives

The aim of this pilot study protocol is to assess the feasibility of a randomised controlled trial to assess the effects of a 3-month probiotics therapy in a cohort of Parkinson’s disease patients. Specific feasibility objectives will be assessed to define the feasibility of the proposed clinical trial, including recruitment, acceptance and dropout rate, and outcome identification, as listed in the following Table 1.

**Table 1 Tab1:** Feasibility objectives

**Objective**	**Description**
Recruitment rate	The number of identified eligible subjects in a given amount of time, at the proposed clinical setting.
Acceptance rate	The fraction of identified eligible subjects who will be willing to participate in the proposed clinical trial.
Dropout rate and safety	Dropout rate will be reported as the fraction of enrolled subjects who will be dropped from the study for any reason. Reported reasons for subject drop-out will be recorded and analysed to confirm safety for both the treatment and placebo administration to enrolled subjects.
Primary outcome identification and sample size estimate	The primary outcome for the future main clinical trial will be identified among significant immune profile changes detected in the pilot trial. Data from the pilot trial will also be used to estimate an appropriate sample size for the main trial.
Secondary outcomes identification	Collected data in the pilot trial will be used to identify promising secondary outcome measures.

Data collected during this pilot study will include the following assessments to evaluate possible outcome measures for the definitive randomised controlled trial:1) Cytokines production (IFN-γ, TNF-α, IL-4, IL-10), as already tested in vitro, to confirm the immune-modulating potential of probiotics.2) Assessment of CD4+ and CD8+ T naïve/memory cells, CD4+ T helper subsets, CD4+ regulatory T cells, monocytes, and NK cells to test the immunomodulating effects of probiotics administration on the immune profile.3) Monitoring of motor and non-motor symptoms of PD, including gut function, and subjective quality of life during the trial period.

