### Eligibility criteria

All included patients will have a diagnosis of Parkinson’s disease with a disease duration between 2 and 5 years at baseline. Exclusion criteria for this study are listed in the following Table 2:

**Table 2 Tab2:** Exclusion criteria

**Condition**	**Exclusion criteria**
Present disease or disease history	Autoimmune disease Inflammatory bowel diseases Past major abdominal or pelvic surgery
Therapy	Immune-modulating or immunosuppressive Antibiotics therapy up to three months before enrolment
Feeding-related conditions	Usage of tube feeding Known or suspected allergy to any treatment or placebo component
Cognitive impairment	Known and established cognitive decline Any comorbidity preventing reliable completion of trial assessments
Parkinson’s symptoms	Motor fluctuations

Patients will be required to report any proposed modification in their medical therapy. Patients who will need substantial changes in antiparkinsonian therapy will be dropped from the trial. The use of laxative or prokinetic drugs will be recorded and is not an exclusion criterion per se, but the introduction of these medications or posology variations should be avoided during the trial.

Since the trial is primarily aimed at confirming the immunomodulating properties of probiotic treatment, any intercurrent and symptomatic infections, inflammatory episodes, or other medical conditions will be recorded. Evaluation by clinical staff for potential patient dropout will be based on the severity and temporal proximity of the event to scheduled visits and blood withdrawal. All participants will be advised to maintain a constant dietary intake and a regular physical activity during the trial. A daily report including quality of life aspects will be requested and evaluated using appropriate clinical scales. Informed consent will be obtained by clinicians after the eligibility assessment and during the first visit. All subjects or their legal representatives will be given all relevant information about the study structure and objectives. Additional consent will be requested for the use of collected data and biological specimens in ancillary studies.

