### Recruitment

Recruitment will occur in Azienda Ospedaliero-Universitaria Maggiore della Carità di Novara. Enrolment will be proposed to eligible subjects by clinical neurologists during routine visits and given their recorded consent to receive information about ongoing research and recruiting trials. Patients will be recruited continuously until reaching the desired sample size and will start the trial period asynchronously. The recruitment period will be limited in time to avoid seasonal diet modifications as a confounding factor for some of the trial outcomes.

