## Discussion

The involvement of the immune system in the development and progression of Parkinson’s disease makes it a promising target for a disease-modifying therapy. This clinical trial will test the ability of probiotics therapy in modulating the peripheral immune system, which in turn is expected to have beneficial effects on disease progression and patients’ quality of life. If this trial shows a potential beneficial role of probiotics in immunomodulating peripheral immunity in PD patients, a trial with a larger cohort could be designed and disease progression could be monitored over a longer period to assess the disease-modifying potential of this intervention.

The possibility to use probiotics as adjuvant therapy in Parkinson’s disease could also help in reducing necessary drugs for the treatment of disease-related symptoms such as laxatives, prokinetics, and others (with a final reduction of individual therapy undesired effects and costs). The results of this study will also point further research in a disease-modifying direction. If further research shows a potential disease-modifying effect of probiotics, treatment could be proposed to all PD patients without any specific risks and increasing the quality of life in these patients.

In our mono-centric setting and considering rigorous exclusion criteria, one possible problem will be the recruitment of a large enough number of subjects. Enrolment will therefore be proposed to all eligible subjects by clinical neurologists during routine visits and given their recorded consent to receive information about ongoing research and recruiting trials. This will help in reaching the maximum number of possible participants, while ensuring strict adherence to inclusion/exclusion criteria, since participation will be only proposed to eligible patients by their neurologist and after a thorough medical evaluation.

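### The recruitment-rate outcome pools patients already in the 2-to-5-year window with new entrants, so projecting it to a larger trial at this centre is likely to understate duration

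*Protocol article*

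**What the plan says.** Recruitment rate is one of the feasibility objectives. Table 1 (Objectives) defines it as "The number of identified eligible subjects in a given amount of time, at the proposed clinical setting". Primary feasibility outcomes puts it into practice by "recording the number of eligible outpatients who scheduled a neurological examination in the proposed clinical setting during the pilot trial". The same paragraph adds the acceptance rate and states the purpose: "Both assessments together will allow for an initial estimate of the needed duration for the main clinical trial".

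Four other statements determine what that count contains:

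- Eligibility criteria requires a "disease duration between 2 and 5 years at baseline", a window three years wide.
- The Discussion says: "Enrolment will therefore be proposed to all eligible subjects by clinical neurologists during routine visits".
- Under Recruitment: "Patients will be recruited continuously until reaching the desired sample size".
- Also under Recruitment: "The recruitment period will be limited in time to avoid seasonal diet modifications", with no length given.

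Neither definition separates patients who were in the window when recruitment opened on 22 November 2021 (Trial status) from those who reached two years of disease, or were referred, afterwards.

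**The concern.** A clinic that starts approaching every eligible patient at routine visits meets first the patients it already follows. They are a stock built up over as much as three years. Once they have been approached, further accrual depends on patients newly crossing two years of disease and on new referrals. A short recruitment period gives a count weighted towards the stock. A larger main trial outlasts that stock and has to rely on the inflow.

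The pooled count cannot tell the two apart, yet it is the input to the duration estimate. Feasibility of the main trial is the pilot's stated aim, and the authors foresee difficulty: "In our mono-centric setting and considering rigorous exclusion criteria, one possible problem will be the recruitment of a large enough number of subjects". A forecast that leans optimistic is unhelpful on exactly that question.

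**Working it through.** The article states no recruitment rate, acceptance rate, recruitment length or main-trial duration, so there is no figure of its own to reproduce. The check asks how far a linear projection of the pooled rate could be off.

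**From the article.** Window of 3 years. Pilot target of at least 80. 40 recruited since 22 November 2021. The writing date is not given but cannot precede the registry update of 18 February 2022, at least 88 days later. Accrual is therefore at most 40/88 × 30.44 = 13.8 per month.

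**Assumed.** Acceptance a = 0.6. Mean time to a visit V = 0.5 or 1 year. Time a patient stays eligible W = 3 or 1.5 years. Main trial of 160, or 320 where stated. Same centre and criteria.

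**Rates.** With inflow L per year, the steady stock is L × W. If everyone eligible is seen within D years and W = 3, the pilot's rate divided by the inflow is about 1 + 3/D: 7.0 for D = 0.5 and 2.5 for D = 2. This compares rates. It is not the error in duration, because a main trial also opens with some stock.

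**Durations.** Let q = 1 − exp(−T/V). Up to T = W, the number of eligible patients seen is

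C(T) = L × [T(2 − q) + q(W − 2V)].

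After that, patients are seen at L × (1 − exp(−W/V)) per year.

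*Case A: stock 200, W = 3, V = 0.5, so L = 66.7.*

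- Pilot: 80/0.6 = 133 must be seen. At T = 0.52, q = 0.6465 and C = 66.7 × (0.52 × 1.3535 + 0.6465 × 2) = 133. The rate is 80/0.52 = 154 per year, or 12.8 per month, within the bound.
- Linear forecast for 160: 160/154 = 1.04 years.
- Main trial opens at once with nobody re-approached: 240 enrolled in all, so 400 seen. C(3) = 333.5, and the other 66.5 arrive at 66.5 per year, taking 1.0 year. Total 4.0 years; the main trial takes 4.0 − 0.52 = 3.48 years. Ratio 3.48/1.04 = 3.3. For 320 the same steps give 7.49/2.08 = 3.6.
- Main trial opens three years later with the pool refilled and everyone open to approach: at T = 2.0, q = 0.9817 and C = 66.7 × (2 × 1.0183 + 0.9817 × 2) = 267, giving 160 enrolled. Ratio 2.0/1.04 = 1.9.

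*Case B: stock 300, W = 1.5, V = 1, so L = 200.*

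- Pilot: at T = 0.56, q = 0.4288 and C = 200 × (0.56 × 1.5712 − 0.4288 × 0.5) = 133. The rate is 80/0.56 = 143 per year, or 11.9 per month. Forecast 160/143 = 1.12 years.
- Refilled pool: at T = 1.35, q = 0.7408 and C = 200 × (1.35 × 1.2592 − 0.7408 × 0.5) = 266. Ratio 1.35/1.12 = 1.2.
- No gap and no re-approach: C(1.5) = 289, and the remaining 111 at 155 per year take 0.71 years. Main trial 1.5 + 0.71 − 0.56 = 1.65 years. Ratio 1.65/1.12 = 1.5.

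A stock of 800 at a = 0.6 and V = 0.5 gives ratios of only 1.1 to 1.9. It also implies about 885/12 = 74 recruits per month in the pilot, which the reported accrual rules out for those values of a and V.

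**Would counting new entrants alone do?** In case A, entrants seen during the pilot number L × [T − Vq] = 66.7 × (0.52 − 0.323) = 13, although 66.7 × 0.52 = 35 entered. At a = 0.6 that is 7.9 willing in 0.52 years, or 15 per year, against a true 66.7 × 0.6 = 40. Unseen stock is about 80, of whom 48 are willing. The raw entrant count forecasts (160 − 48)/15 = 7.5 years. The true inflow plus remaining stock gives (160 − 48)/40 = 2.8 years. The modelled duration is 3.48 years and the pooled forecast 1.04.

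**The case against.** A reader might infer that the pilot is a single sweep of the clinic and that its forecast will certainly be several-fold too short. The article does not support that. Recruitment stops at the target, so unseen patients may remain, and new patients enter the window throughout. The factors of 2.5 to 7 above are ratios of rates, not errors in duration. Nothing bars pilot participants or refusers from the main trial, and its size, start date, number of sites and eligibility window are not fixed. The other exclusions, such as motor fluctuations and recent antibiotics, may shorten the time a patient stays eligible. That raises inflow relative to stock and shrinks the bias, as case B shows.

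It is also fair to say that the article calls the result only an initial estimate, does not state that the rate will be projected linearly, sets no threshold for going ahead, and condenses a fuller protocol.

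These points limit the size and the certainty. They do not remove the concern. The measure and its use are both written in the article, and both are tied to the proposed setting and the proposed criteria. No same-centre, same-criteria case tried here reversed the direction.

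**Conclusion.** The concern holds in a limited form. The recruitment-rate outcome mixes existing stock with inflow. If that pooled rate is projected to a larger trial at this centre with the same criteria, duration is likely to be understated. Under the assumptions above, and with accrual of no more than 13.8 per month, the worked ratios of true to forecast duration run from 1.2 to 3.6, so near 1 to about 4 is a fair summary. A wider set of assumptions reached about 5. The ratio falls with slower visits, shorter time eligible, a longer gap before the main trial and freedom to re-approach patients. It rises with a small stock largely used by the pilot and with a larger main trial. None of these quantities is in the article, so no single factor should be quoted. A multicentre main trial or a changed window would need its own forecast.

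**What to change.** In Table 1 and Primary feasibility outcomes:

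1. Count each eligible outpatient once, however many appointments are scheduled.
2. Report eligible patients by calendar month, split by whether they were already in the window on 22 November 2021 or entered it or were referred later.
3. Estimate yearly inflow from the onset dates of all eligible patients identified (the number crossing two years of disease per year) plus new referrals, allowing for patients not yet seen. Do not use the raw count of new entrants who happened to attend during the pilot, which is too low for the reason shown above.
4. Base the duration estimate on that inflow plus the estimated remaining stock, and give a range. State whether pilot participants and refusers may be approached again.

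Disease duration is already needed to judge eligibility, so no visits are added, and the split can be applied to the 40 already recruited. The cost is a little more analysis and an accrual forecast that is less favourable and less precise.

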#### Patient-centred outcomes

A significant variation in scores resulting from appropriate questionnaires and scales will be evaluated as an outcome measure for exploratory and patient-centred endpoints (variations in motor and non-motor symptoms from T0 to T1 and T2).

### Participant timeline

The timeline of the proposed study is summarised in the following Table 4. Each patient will be visited within 2 weeks before starting the proposed treatment to assess eligibility and collect informed consent. Treatment with probiotics or placebo will then be started (T0) and carried out for 12 weeks, when the administration will be stopped and final assessments will be performed (T2). An additional interim assessment is scheduled at 6 weeks after T0 (T1).

**Table 4 Tab4:** Participant timeline

**Visit**	Enrolment	T0	T1	T2
Time Point	Within 2 weeks before T0	T0	6 weeks after T0	12 weeks after T0
Informed consent	X			
Physical/neurological examination	X	X	X	X
Vital signs	X	X	X	X
Unified Parkinson’s disease rating scale (UPDRS)		X	X	X
Hoehn and Yahr assessment (H&Y)		X	X	X
Zung self-rating anxiety scale		X	X	X
Beck depression inventory scale (BDI-II)		X	X	X
Composite autonomic symptoms scale-31 (COMPASS 31)		X	X	X
Montreal cognitive assessment (MOCA)		X		X
PAC-QOL		X	X	X
Non-motor symptoms scale (NMSS)		X	X	X
Wexner scale		X	X	X
Constipation assessment scale (CAS)		X	X	X
Bristol stool form chart		X		X
Blood withdrawal		X		X
Treatment/placebo delivery		X		

### Sample size

The design of this pilot study is explorative and equally randomised to treatment with probiotics or placebo. Due to the exploratory nature of the proposed study, a formal sample size calculation is not strictly required [18]. In our precedent in vitro study, statistically significant results were found in a small cohort of 40 PD patients for all tested probiotic strains, with a global reduction in proinflammatory cytokines production and an increase in anti-inflammatory cytokines. Doubling this sample size, with at least 80 specimens to be collected at both T0 and T2, will allow us to correctly evaluate the feasibility of the future main study.

We thus used data from the said study to estimate sample sizes for the in vitro effect of all tested probiotic strains and a sample size of 80 subjects allows for the determination of most tested cytokines variations with an expected power greater than 80%, setting our threshold for statistical significance at 0.05.

As previously stated, the drop-out rate of this pilot study will also be recorded and used to determine an appropriate sample size increase for the main study.

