**Methods:**

This is a pilot randomised placebo-controlled clinical trial protocol for a 12-week treatment with probiotics. At least 80 patients affected by PD will be recruited and randomly allocated to either the treatment or placebo group in a 1:1 ratio. General inclusion criteria will be the onset of PD 2 to 5 years before the trial and absence of autoimmune comorbidities or immunomodulating therapy. Our primary endpoint is the assessment of changes in extracellular cytokine levels (Interferon (IFN)-γ, tumour necrosis factor (TNF)-α, interleukin (IL)-4, and IL-10) and ROS production. Secondary outcomes include changes in lymphocyte subpopulations and transcriptional factors mRNA levels.

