### Brief description of protocols for endpoint assessment

#### Plasma cytokine measurement

The possible influence of probiotic treatment on the inflammatory profile will be evaluated by measuring at T0 and T2 the plasma levels of pro (e.g., TNF-α, IFN-γ) and anti-inflammatory cytokines (IL-10, IL-4). To this end, at each visit time, plasma aliquots from every sample will be separated and stored for cytokines assays (ELISA Ready-SET-Go! Affymetrix eBioscience, USA). Two milliliters of fresh blood will be centrifuged at 1400g for 10 min at room temperature and two plasma aliquots of 350 µL each will be stored in 1.5mL vials to assay extracellular cytokines levels.

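### The power above 80% claimed for 80 subjects comes from an in vitro effect; it is unsupported and not reproducible for a 40-versus-40 comparison of plasma cytokines

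*Protocol article*

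**What the plan says.** The Sample size section of the protocol article calls the study exploratory and says that a formal calculation is not strictly needed. It then makes two separate statements.

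- **Feasibility.** The earlier in vitro study found significant results in 40 patients. "Doubling this sample size", "with at least 80 specimens to be collected at both T0 and T2", is said to be enough to evaluate the feasibility of the main study.
- **Power.** Data from that study were used to estimate sample sizes for the in vitro effect of the tested strains, and "a sample size of 80 subjects allows for the determination of most tested cytokines variations with an expected power greater than 80" per cent, "setting our threshold for statistical significance at 0.05".

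No effect size, SD, test, sidedness or number per arm is given.

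Other sections describe a different measurement and comparison. The Background describes the earlier study as work on peripheral blood mononuclear cells. Under Plasma cytokine measurement, plasma aliquots are taken at T0 and T2 "to assay extracellular cytokines levels". Trial design gives 1:1 allocation. Primary feasibility outcomes looks for significant variation between the two arms and says that whether the in vitro properties are confirmed in vivo is still to be tested.

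The abstract gives the number as "At least 80 patients affected by PD will be recruited and randomly allocated".

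**The concern.** A power statement describes a particular effect, SD, test and design. Here the effect and SD come from probiotics acting on blood cells outside the body. The trial asks whether plasma concentrations change differently in two arms after oral treatment. Nothing in the article links the two quantities, and the protocol itself treats the in vivo effect as an open question.

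This matters even in a pilot. Table 1 says that the main trial's primary outcome will be chosen from the significant immune changes seen here. If readers believe that most cytokines were tested with more than 80% power, a non-significant cytokine may be discarded as adequately tested when the trial had little chance of detecting a realistic difference.

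**Working it through.** **Inputs from the document.** Total of 80, allocation 1:1, hence 40 per arm; threshold 0.05; claimed power above 80%.

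**Assumptions.** Two-sided test; t-test on the T0-to-T2 change, with differences expressed in SDs of that change; any loss rate. The document gives none of these as inputs to its power figure. Statistical methods also allows rank tests, so the t-test results are benchmarks.

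**1. Reproducing the stated figure.** Not possible, because the effect size, SD, test and pairing are all missing. The calculation has to be inverted: what difference would 80 subjects detect?

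**2. Detectable difference, 40 versus 40.** In SD units the standard error is √(2/40) = 0.2236. The normal approximation gives (1.960 + 0.842) × 0.2236 = 0.626. The noncentral t gives 0.634. So 80% power is reached at about 0.63 SD.

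**3. Power at other true differences.** Power ≈ Φ(d/0.2236 − 1.96):

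| True difference d (SD) | Power, 40 per arm |
|---|---|
| 0.3 | 27% |
| 0.4 | 43% |
| 0.5 | 61% |
| 0.6 | 77% |
| 0.7 | 88% |
| 0.8 | 95% |

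The claim would be true for differences above about 0.63 SD and false below. The document does not say where the in vivo effect lies.

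**4. Illustration if the in vitro contrast was within donor (assumption).** In a paired test the standardised effect with 80% power is 0.454 for 40 pairs and 0.317 for 80 pairs (noncentral t). The same standardised effects at 40 versus 40 have 51.8% and 28.8% power. The reason is the standard error: √(1/40) = 0.158 for 40 pairs against √(2/40) = 0.224 for two arms of 40, a ratio of √2 at equal SD of change.

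**5. Precision.** The 95% CI half-width for a between-arm difference is 1.96 × 0.2236 = 0.44 SD.

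**6. If 80 means randomised.** With an assumed 15% loss, 40 × 0.85 = 34 per arm, and the detectable difference is 0.69 SD (noncentral t). Keeping 80 evaluable at that loss would need 80/0.85 = 94.1, so 95 randomised.

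**7. Precision of a feasibility rate.** For illustration, 12 dropouts in 80 is 15%, with an exact (Clopper-Pearson) 95% CI of 8.0% to 24.7%.

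**The case against.** The best defence is that this is a declared exploratory pilot. It says that no formal calculation is required, discloses the in vitro source openly, and has feasibility, outcome selection and sizing of the main trial as its aims. No confirmatory test rests on the figure. That limits the consequence but does not rescue the sentence: once a numerical power is stated, it should describe this trial.

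Four stronger readings are tempting, and the document does not support them.

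- **That the power claim is false.** Without an effect size or SD this cannot be shown. A true difference above about 0.63 SD would give more than 80%. The 52% and 29% figures assume a within-donor contrast lying exactly at 80% power, whereas the text says above 80% and does not say whether its calculation was paired. They illustrate; they do not measure an error.
- **That doubling 40 to 80 was meant to convert a paired design into a parallel one.** The text ties the doubling to feasibility; the power statement stands in a separate paragraph.
- **That dropouts were forgotten.** The target of 80 specimens at both T0 and T2 can be read as 80 completers, and Recruitment continues until the desired size is reached. Set against the abstract's 80 randomised, this is an ambiguity and no more.
- **That the threshold should have been split over five outcomes.** The power sentence concerns cytokines taken singly, and ROS is outside it. Adjustment in an exploratory pilot is a matter of preference.

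**Conclusion.** The concern stands in this form: the stated power is unsupported for the between-arm comparison of plasma cytokines and cannot be reproduced from the article. That conclusion follows from the protocol's own account of where the figure came from and needs no assumption about the missing inputs.

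The size of the discrepancy is unknown. Under a two-sided t-test at 0.05, unadjusted, with 40 evaluable per arm, power is 27% at 0.3 SD and 95% at 0.8 SD, so the claim depends entirely on an in vivo effect that the protocol has yet to establish. It is separately unclear whether 80 counts patients randomised or patients with blood at T2.

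**What to change.** Change the Sample size text; no increase in N is proposed.

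1. Remove the in vitro power claim.
2. State that 40 evaluable patients per arm give 80% power at two-sided 0.05 (t-test) for a between-arm difference of about 0.63 SD of the change score, per outcome and unadjusted, with a 95% CI half-width of about 0.44 SD.
3. State that the trial is not powered on in vivo effect data, so a non-significant cytokine must not be treated as adequately tested when the main trial's primary outcome is chosen.
4. Say whether 80 means randomised or evaluable at T2. If randomised, add the detectable difference under a stated assumed loss, for example 0.69 SD at 34 per arm with 15% loss.
5. Justify 80 by the precision of the feasibility rates, for example the interval of 8% to 25% around 12 dropouts in 80, marked as an illustration.

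The cost is a few sentences and a less favourable-looking figure. Recruitment, design and analysis are unaffected.
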